## Methods/Design

### Ethics approval

This study is registered with the Australian New Zealand Clinical Trials Registry (ACTRN12613000105741) and approved by the Queensland Children’s Health Services (Royal Children’s Hospital) Human Research Ethics Committee and The University of Queensland Ethics Committee.

### Study design

This study is a prospective, randomised controlled trial. Participants will be randomised to receive one of three commonly used dressings for burn wounds, (1) Acticoat™, (2) Acticoat™ and Mepitel™ combined or (3) Mepilex Ag™, in order to determine the effects of the dressings on pain and the rate of re-epithelialisation in acute, partial thickness burns in children. It is hypothesised that silver dressings with a silicone interface, compared to no silicone interface, will decrease the time to re-epithelialisation of a burn injury and decrease the amount of pain and distress experienced during dressing changes within a paediatric population. The design of data collection is displayed in Figure 1.

**Figure 1 F1:**
[figure not shown]
**Data collection flowchart.** The chronological timing and order of data collection within the burn wound care procedure framework.

### Study setting

Participants for this study will be recruited from the Royal Children’s Hospital, Brisbane, Australia. Children presenting to the Department of Emergency (DEM) from March 2013 will be screened on presentation by a surgical registrar for eligibility to this study.

### Participants

#### Inclusion criteria

Children who are aged 0 to 15 years with an acute partial thickness (superficial partial to deep partial thickness inclusive) burn injury and a burn total body surface area of ≤10%, presenting at the DEM within the first 72 h post-injury will be considered for inclusion in this study.

#### Exclusion criteria

Children will be excluded from this study if they present >72 h post burn; have received silver dressings prior to presentation at the Royal Children’s Hospital; have sustained a superficial (erythema only) or full thickness burn; have sustained a chemical or friction burn; present with cold, flu or viral symptoms (e.g. upper respiratory tract infection); have received inappropriate first aid (e.g. dirty water); have a known reaction to silver products; are non-English speaking; have a cognitive impairment; or are currently involved with Department of Communities (Child Safety). Additionally, any children who have burn wounds requiring grafting, contract an infection or need to change dressing type during the course of their treatment will only have data collected up until that point in time, as these changes in clinical care will void the intervention they have been randomised into for the study. These exclusions will not be known until after the child is recruited and randomised because of the variability of patient and wound management needs.

Apart from the dressings received, children participating in this study will receive the same standard medical care as those children not participating in the study.

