#### Grafting

A note will be recorded if a participant’s wound requires grafting. Data collection will cease on that date for the participant as different dressings are used for wounds that are grafted; however all data preceding that point will be included for analysis.

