#### Scar assessment

If further scar management treatment is required after full re-epithelialisation of the burn injury has occurred, a referral will be made by the treating consultant to the scar management clinic. At 3 months following full re-epithelialisation of the burn injury, a face-to-face follow-up will be completed with all participants to conduct a skin and/or scar review in conjunction with Occupational Therapy. An ultrasound scan (BT12 Venue 40 MSK, GE Healthcare) [19] will be taken of the burn area to measure the height of the scar, and digital and 3D photographs will also be taken. The Patient and Observer Scar Assessment Scale will also be completed with the child (if over the age of 6 years) and/or caregiver. All scar management resources used with the participant will be recorded for a cost-analysis. At 6 months post-full re-epithelialisation, the same measures will be repeated.

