### Discontinuation/adverse events

The infection of the burn wound is a potential adverse effect of any of the burn dressings. Infection rates at our burn centre are extremely low; however if any adverse effects such as infection occur, participants will only have data collected up until that point in time analysed, as clinical care (including dressing type) may change to address the adverse event. Additionally, if a consultant feels that a particular dressing is not appropriate for a participant’s care, they may change to a different dressing. If this occurs, data collection for this participant will cease from this date. All data preceding this date will be included for analysis.

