#### Data analysis

All statistical analyses will be conducted using SPSS 21 (IBM Corp., Armonk, NY, USA). Generalised linear models, estimating variance appropriately for repeated measures, will be used to determine whether there are differences among the Acticoat™ group, the Acticoat™ combined with Mepitel™ group and the Mepilex Ag™ group in primary and secondary outcomes. Changes in the intervention effects will be examined with burn depth, burn total body surface area, mechanism of injury, anatomical location of the burn, skin type, ease of dressing removal and application and physical function considered a priori to be of potential interest. All data will be analysed as intention to treat and on a per protocol basis, with the intention to treat analysis being the primary approach for this trial. Any missing data will be handled using the multiple imputation method. All tests will be two-tailed and only those with a *p* value <0.05 will be considered statistically significant.

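### Outcome data end at infection, dressing change or grafting, so the intention-to-treat analysis named as primary has no observed healing time for those children and rests on imputation alone

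*Protocol article*

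**What the plan says.** The Data analysis section plans both an intention-to-treat and a per-protocol analysis, "with the intention to treat analysis being the primary approach for this trial", and assigns missing data to multiple imputation. The Sample size section names days to re-epithelialisation as the primary outcome.

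Three other sections limit the data of children already randomised:

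- **Exclusion criteria:** children who need a graft, become infected or "need to change dressing type during the course of their treatment will only have data collected up until that point in time". The stated reason is that the change in care voids the randomised intervention. The section adds: "These exclusions will not be known until after the child is recruited and randomised".
- **Grafting:** "Data collection will cease on that date for the participant as different dressings are used for wounds that are grafted". Earlier data are kept.
- **Discontinuation/adverse events:** after an adverse event such as infection, "participants will only have data collected up until that point in time analysed". If the consultant changes the dressing: "If this occurs, data collection for this participant will cease from this date". Earlier data are again kept.

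The Scar assessment section, however, says that at 3 months after healing "a face-to-face follow-up will be completed with all participants", with the same measures at 6 months. Scar-management resources feed the cost analysis.

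**The concern.** Intention to treat compares children by randomised arm whatever happens to them afterwards, and so needs outcomes recorded after a departure from the assigned dressing. Here recording ends, or later data are set aside, at exactly that departure. The observed data are therefore on-treatment data and differ little from the per-protocol set.

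The stopping events are not neutral. Grafting and infection are plausibly signs of a wound doing badly, and the Background itself says infection can delay re-epithelialisation. A switch is decided by a consultant when the dressing is thought unsuitable, and the Blinding section says the dressing cannot be completely masked. All three events may therefore differ by arm. What is at stake is the primary healing comparison, the scar comparison and the cost analysis. An analysis plan cannot repair this later, because photographs, tracings and scar reviews that were never taken cannot be recreated.

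**Working it through.** **1. What each rule leaves**

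| Event after randomisation | Kept | Not available |
|---|---|---|
| Infection | the event itself; pain, wound area and resources up to it | days to re-epithelialisation, 3- and 6-month scar result, later costs |
| Dressing change | measures up to the change | the same |
| Grafting | the event itself; measures up to it | the same; in addition, no section shown says what value a grafted child takes for days to re-epithelialisation |

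The scar visits are timed from full re-epithelialisation and promised to all, so that section and the three stopping rules cannot both be followed.

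**2. What imputation can do.** Earlier wound areas can inform it. Standard multiple imputation assumes data are missing at random. As no child is observed after an event, the imputation model is fitted to children still on their dressing. The filled-in healing time is what would be expected had the child stayed on it, which is not the intention-to-treat quantity.

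**3. The plan's own figure.** Inputs from Sample size: SD 4, difference 3 days, two-sided α 0.05, power 80%.

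n = 2 × SD² × (z₀.₉₇₅ + z₀.₈₀)² / difference² = 2 × 16 × (1.960 + 0.842)² / 9 = 27.9, so 28 per arm (power 80.1%). The stated 28 reproduces. The planned total of 100 gives 100/3 = 33.3 per arm.

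**4. Illustration.** The documents give no event rates, so the loss pattern is assumed: true means 15 and 18 days, SD 4, normal, every child unhealed at day 21 lost, and only children with an observed healing date analysed.

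With z = (21 − mean)/4 and λ = φ(z)/Φ(z): proportion lost = 1 − Φ(z); remaining mean = mean − 4λ; remaining SD = 4√(1 − zλ − λ²).

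- Mean 15: z = 1.50, λ = 0.139; 6.7% lost; mean 14.44; SD 3.52.
- Mean 18: z = 0.75, λ = 0.389; 22.7% lost; mean 16.44; SD 2.98.
- Observed difference: 16.44 − 14.44 = 2.00 days.

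Power ≈ Φ(difference/SE − 1.96):

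- From 28 per arm: 26.1 and 21.7 remain; SE = √(3.52²/26.1 + 2.98²/21.7) = 0.94; 2.00/0.94 = 2.12; power about 57%.
- From 33.3 per arm: 31.1 and 25.8 remain; SE = 0.86; ratio 2.32; power about 64%. With no loss at all, SE = 4√(2/33.3) = 0.98, ratio 3.06, power about 86%.

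**5. Sensitivity to the assumption**

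- Cut at day 18: difference 1.37 days. Cut at day 24: 2.57 days.
- Half of those unhealed at day 21 lost: about 2.6 days.
- Only the slower arm loses its slowest 5%, 10% or 20%: its mean falls by 4φ(z)/(1 − fraction lost) = 0.43, 0.78 or 1.40 days. A true 3-day difference becomes 2.57, 2.22 or 1.60. Two equal dressings would show a false advantage of 0.43, 0.78 or 1.40 days for the arm with losses.
- Equal fractions of the slowest lost in both arms: the difference stays 3.0 days, though both means are too low.

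**The case against.** The case for the plan is substantial in several respects.

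- **Imputation is planned.** A reader might infer that intention to treat cannot be done at all. The documents do not support that: all randomised children can be analysed by arm, with wound measurements up to the event feeding the imputation. What stands is that this is intention to treat in name only.
- **The children are not erased.** A reader might infer that the worst healers drop out of the trial's results. They do not: data before the event stay in, and grafting and infection are secondary outcomes, so an excess in one arm would be visible there. Their records are cut short, which still removes the primary, scar and full-cost values.
- **The events may be few.** The protocol calls infection extremely low at the centre. It says nothing comparable of grafting or switching, and deep partial thickness burns are eligible.
- **The illustration is severe.** Slow healing alone is not a stopping trigger, no section stops data at a fixed day, and the figures ignore imputation. The 57% takes losses from 28 per arm although 100 children are to be recruited; the plan does not say whether stopped children fall within its 20% loss allowance.
- **Direction is not established.** A reader might infer that a poor dressing must look better. That needs loss to differ by arm, which is plausible but not shown.
- **Grafting is different.** After a graft, spontaneous healing can no longer be observed, so ending healing measurements there is defensible. The gap is the undefined primary value and the lost scar and cost follow-up.

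**Conclusion.** The point stands as a contradiction in the protocol's own text. The rules in Exclusion criteria, Grafting and Discontinuation/adverse events do not fit intention to treat as the primary approach, nor scar review of all participants. For a child stopped before healing there is no observed primary outcome, and imputation rests on an assumption that the stopping events make doubtful and that no collected data can test.

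Confidence is high for the contradiction and low for the size of any bias. A 3-day difference falling to 2.0 days, with power of 57% to 64%, is a severe complete-case illustration under an assumed day-21 cut. Other assumed patterns give 1.4 to 2.6 days, and equal loss fractions give no bias in the difference. It should be corrected because uncollected outcomes cannot be recovered at analysis.

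**What to change.** - In Exclusion criteria and Discontinuation/adverse events, replace the stopping rule with continued outcome recording for every randomised child after infection or dressing change: healing, resource use, and the 3- and 6-month scar reviews. Analyse by randomised arm. Restrict data to the period before the event only in the per-protocol analysis.
- In Grafting, continue scar and cost follow-up, and state from which date the scar visits are counted. State how a grafted child enters days to re-epithelialisation, for example with grafting as a competing event, or as not healed, in a time-to-event analysis.
- Reconcile Scar assessment with these three sections.
- For children already stopped, take the healing or graft date from the chart where consent allows.

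**Cost.** A short amendment and some extra data entry. Dressing changes already take place at the same burn centre, so healing data should need few or no added visits. The scar reviews, with ultrasound, are real work for children now stopped, but are already promised to all. The primary result will include care given after a switch; the per-protocol analysis complements it. No change to clinical management is proposed.

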### Recruitment

A surgical registrar will be notified of a patient with a burn injury by DEM staff and will then determine the patient’s eligibility according to study criteria. The potential participants and their parents/caregivers will be notified of their eligibility to participate in this study by the registrar. Parents/caregivers will then be asked if a member of the research team can speak to them about the study. Informed caregiver consent and child assent (for children 6 years and above) will be gained by an investigator on the study after a discussion with the child and their caregiver regarding the information in the Patient Information Sheet. Once consent has been gained, the investigator will randomise the patient to one of the three dressing treatment arms. Randomisation will be completed using a computerised random number generator and randomisations will be enclosed in sealed, opaque envelopes by an independent party. All dressings will be carried out by staff experienced in burn dressing application. Baseline measures (pain and behavioural scores from child, nurse and parent, pulse rate and respiratory rate) will be recorded by the primary investigator prior to and after the dressing has been applied. The patient will then present at our burn centre every 3–4 days for subsequent dressing changes. Any analgesia given to the patient will be recorded.

The first 3 days post-burn injury often have the highest risk of toxic shock syndrome, which can be potentially fatal if left untreated [10,18]. While the incidence rate of toxic shock syndrome at our burn centre is extremely low to non-existent, phone calls will be made to each participant by the primary investigator within this period. A set of standardised questions will be used to screen for any toxic shock syndrome symptoms and to assess how the child and their parents or caregivers are managing the dressing, and all responses will be recorded.

### Intervention

The intervention will be one of the Acticoat™, Acticoat™ combined with Mepitel™ or Mepilex Ag™ dressing arms that the participant is randomised into on presentation. This dressing will then be used to treat the burn wound and will be replaced every 3–4 days at each dressing change until re-epithelialisation occurs or grafting is required. The dressings will be applied according to the manufacturer’s instructions.

### Data collection

Demographic information and clinical details will be obtained from the caregiver and the patient’s chart regarding the mechanism of the burn injury, site of the injury, total body surface area of the burn and first aid the patient received. Children over the age of 4 years will be given the Ditto™ (virtual reality) device (Diversionary Therapy Technologies, Queensland, Australia) to engage in the “Bobby got a Burn” procedural preparation story at their first dressing change. These children may also engage in a choice of games or stories on the Ditto™ during all dressing changes. At the first dressing change only, each participant will have their burn/s scanned using the LDI2-BI (VR) Laser Doppler Imager (LDI) (Moor Instruments, Axminster, Devon, UK), which measures wound depths (in blood perfusion units) as a percentage of total wound area. The laser Doppler imager scan will provide an objective assessment of burn depth to enable a comparison of treatment group demographics [19]. Participants who have burn wounds on different body parts will have separate scans completed for each body part involved. If burn wounds are circumferential or across curved areas, more than one scan will be taken at the frontal, lateral and medial aspects to obtain an accurate scan. In addition, blinded photo reviews of burn depth will be undertaken by a panel of burn specialists (consultants and nurses).

At each dressing change appointment, pain, behaviour and physiological measures (pulse rate and respiratory rate) will be taken before and after dressing removal and before and after the re-application of a new dressing. The time taken for the dressing removal, cleaning and re-application procedure, the number of nurses required to complete the entire procedure, quantity of dressings used and analgesia given to the participant will be recorded. A tracing of the wound using Visitrak™ grids (Smith & Nephew, Hull, UK) and a photograph using the 3D LifeViz Camera (Quantificare, Cedex, France) will be taken. Nursing staff treating the child will be surveyed on a 5-point Likert scale regarding the ease of use of the dressing for that particular child. Parents or caregivers and children over the age of 8 years will be surveyed on a 5-point Likert scale regarding their physical function while wearing the dressing.

All participants in the study will have their dressings changed every 3–4 days at our burn centre as a standard measure. This protocol will be followed until full re-epithelialisation of the wound occurs or grafting of the wound is required [20]. After full re-epithelialisation occurs, participants will be followed up at 3 months and then 6 months to assess skin appearance and/or the presence of scarring.

### Primary outcome measures

#### Days to re-epithelialisation

The number of days from the burn injury date until wound re-epithelialisation occurs, surface area of the wound and percentage of wound re-epithelialisation will be calculated by four methods: (1) clinical judgement from the consultant; (2) use of Visitrak™ grids; (3) 3D camera photographs and analysis on specialist computer software; and (4) blinded review of the 3D photographs by a panel of burn specialists (consultants and nurses).

The 3D photographs and Visitrak™ tracings will be taken of a participant’s burn wound at every dressing change. A ruler will be included in all 3D photographs for measurement calibration in the associated software package Dermapix™ (Quantificare, Cedex, France). The 3D photographs will be analysed by the primary investigator on the Dermapix™ software programme to calculate the burn wound surface area and area of re-epithelialisation of the wound from each dressing change. The Visitrak™ will also be used to trace around total burn area and re-epithelialised areas of the burn wounds at each dressing change in order to calculate wound surface area and percentage of re-epithelialisation.

A blinded review of the 3D photographs will be undertaken by a panel of burn wound specialists (consultants and nursing staff) who will assess the progress of re-epithelialisation and appearance of each participant’s burn wound after data collection has been completed.

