### Blinding

The dressing used for each participant cannot be completely masked, as the Acticoat™ dressing stains the healthy skin around a burn wound brown. The expert panel of burn wound specialists will be blinded where possible; however the primary investigator and expert panel may still be able to deduce what dressing a participant received. The primary investigator will also be present when dressings are being applied and removed to obtain pain scores from the participant, caregiver and nursing staff, and will see which dressing is being used on the child. Wherever possible during data collation and analysis, treatment groups will be de-identified.

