### Statistics

#### Sample size

The primary outcome measure will be days until wound re-epithelialisation. Previous data in paediatric burn patients demonstrated re-epithelialisation within 15 (SD = 4) days and a minimally clinically important difference is 3 days [6]. Thus sample size was calculated at 28 per group at 80% power with an α of 0.05. Allowing for 20% loss to follow-up, a total of 100 participants will be required. The burn centre treats 800 children per year with burns so recruitment for this study should be achievable within 1 year. This sample size will also be adequate to find a significant difference in data collected from pain scores, powered on data from a previous study [6].

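### The primary healing date can be taken from four unranked readings, and only one of them is meant to be blinded

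*Protocol article*

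**What the plan says.** The Sample size section names one outcome: "The primary outcome measure will be days until wound re-epithelialisation". The trial is sized on it, with a mean of 15 days, SD 4 and an important difference of 3 days.

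The section Days to re-epithelialisation treats three quantities together: days from injury to healing, wound surface area, and percentage healed. It says that the "percentage of wound re-epithelialisation will be calculated by four methods". The four are the consultant's clinical judgement, Visitrak tracing, software analysis of 3D photographs, and a blinded review of those photographs by a panel of burn specialists. None is ranked first, and there is no rule for combining them or settling disagreement. The Data analysis section does not choose one.

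On who reads what:

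- **3D software:** "The 3D photographs will be analysed by the primary investigator on the Dermapix™ software programme". The Blinding section says that this person attends the dressing procedures and "will see which dressing is being used on the child".
- **Consultant:** assesses the wound clinically at each dressing change (Infection section). Under Discontinuation/adverse events, "if a consultant feels that a particular dressing is not appropriate for a participant’s care, they may change to a different dressing".
- **Visitrak:** traced on the child at each dressing change. No operator is named and nothing is said about blinding.
- **Panel:** reviews the photographs after data collection ends and is blinded as far as possible. Even so, "the primary investigator and expert panel may still be able to deduce what dressing a participant received".

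The Blinding section adds that groups will be de-identified during data collation and analysis where that can be done.

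**The concern.** Healing is judged largely by eye at discrete visits, and dressings cannot be fully masked. The stated hypothesis is directional: dressings with a silicone interface should heal faster. A reader who knows the dressing and holds that expectation can move a borderline call by a visit.

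If the protocol does not say which reading is primary, two things follow. The analysed date may be one made with knowledge of the dressing, although a blinded reading is planned. And where readings disagree, the choice can be made after results are seen. De-identifying groups at the analysis stage helps with neither a call made at the bedside nor a reader who has already watched the dressing being applied.

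**Working it through.** **1. The plan's own figure.** Inputs from the Sample size and Data analysis sections: difference 3 days, SD 4, 80% power, two-sided α 0.05.

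n per group = 2 × (1.960 + 0.842)² × 4² / 3² = 2 × 7.85 × 1.778 = 27.9, so 28.

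This reproduces the stated 28 (power at 28 per group: 80.1%). The sample size arithmetic is not at issue, and naming one reading as primary does not alter it.

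**2. What is documented about each reading.**

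| Reading | Reader | Knowledge of dressing |
|---|---|---|
| Consultant judgement | Consultant | Not stated, but near certain: this role judges whether the dressing suits the child |
| Visitrak | Not named | Not stated; done at the dressing change |
| 3D software | Primary investigator | Stated: sees the dressing |
| Photograph panel | Burn specialists | Blinding intended; may fail |

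So one reading is explicitly unblinded, one is unblinded by strong inference, one is undocumented, and one is meant to be blinded.

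**3. How far one call can move a date.** Dressing visits are 3–4 days apart. One visit early or late moves that child's date by 3 to 4 days, or 3/3 = 1.0 to 4/3 = 1.3 times the important difference. This is one child's shift, not a shift in the group mean, so a share of children must be assumed to go further.

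**4. Effect on the group mean (assumed shares).** Let a share p of one arm be moved one visit, all in the same direction, with a mid-range interval of 3.5 days. Bias = p × 3.5. For one pairwise comparison with SD held at 4 and 28 per arm, SE = 4 × √(2/28) = 1.07 days. The two-sided type I error is then Φ(−1.96 + bias/SE) + Φ(−1.96 − bias/SE).

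| Assumed share | Bias (days) | Share of the 3-day target | Type I error |
|---|---|---|---|
| 10% | 0.10 × 3.5 = 0.35 | 12% | about 6% |
| 20% | 0.20 × 3.5 = 0.70 | 23% | about 10% |
| 30% | 0.30 × 3.5 = 1.05 | 35% | about 17% |

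**5. Effect of choosing among readings (assumed).** If all four dates were tested and the most favourable reported, with no true effect, the chance of at least one p < 0.05 would be 1 − 0.95⁴ = 18.5% for independent readings. Readings of the same wound will be correlated. Simulating a three-arm one-way ANOVA with 28 per arm (20,000 runs) gave about 16% at correlation 0.5, 11.5% at 0.8, 9.5% at 0.9 and 8.2% at 0.95. The documents give no correlation and do not say that a best-of-four choice would be made.

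**The case against.** The strongest reply is that the sentence is loose. It ties four methods to three quantities, and the text that follows gives Visitrak and the software the job of measuring areas and percentages, while the panel assesses progress and appearance. Four competing healing dates are therefore possible but not certain, and a fuller protocol or analysis plan may settle the matter. Part of this stands: the documents do not establish that four primary results will be reported. But which measurement defines the primary endpoint is protocol content. The article covers the derivation at length, and as written it applies all four methods to the number of days.

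Several stronger readings are tempting and are not supported:

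- *Three of the four readers know the dressing.* This is explicit for the primary investigator only. It is a close inference for the consultant and unknown for Visitrak.
- *The consultant's date will be used by default.* Nothing in the documents says so.
- *Nothing is done to protect the panel.* The panel is to be blinded where possible and groups de-identified where possible. Image coding or cropping is detail that an article may omit.
- *Staining reveals the arm.* Acticoat is in two of the three arms, so staining as described would not by itself identify the arm, and the documents do not say how visible it is in photographs. They do concede that the dressing may be deduced.
- *A one-visit shift exceeds the important difference.* At a 3-day interval it equals it.
- *The 0.35–1.05 days is an estimate.* It is only what the assumed shares imply. A 5% share gives 0.05 × 3.5 = 0.18 day.

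One objection bears on the remedy and stands. Dressing visits, and so the photographs taken at them, run only until the wound is taken to be healed, and the next planned review is at 3 months. If the treating team's call ends the visits, the panel has no later image for a child it would still rate unhealed. A healed wound also has no open margin to crop to.

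**Conclusion.** The concern holds in this form: the outcome that sizes the trial is to be calculated by four methods with no order of precedence, and the only one meant to be blinded is not named as primary. This leaves room for unblinded judgement, or choice among readings, to affect the primary comparison. It does not show that either will happen.

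What rests on the documents alone is the absence of a ranking, the unblinded software reading, the conceded weakness of the panel's blinding, and the fact that one visit is worth at least 3 days for the child concerned. The size of any bias in the mean (0.35–1.05 days, with type I error of about 6–17%) assumes that 10–30% of one arm is moved one way by 3.5 days. The 8–16% false-positive range assumes correlations of 0.95 to 0.5 and selection of the best result. This should be corrected before analysis. It does not invalidate the design, because a reading intended to be blinded is already planned.

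**What to change.** 1. Name the panel's reading as the primary healing date, defined as the first visit at which the panel rates the wound re-epithelialised, and state how panel members' ratings are combined.
2. Make the consultant, Visitrak and 3D-software dates sensitivity analyses.
3. Code the images before review and, where feasible, crop or mask stained skin around the wound while keeping the calibration ruler.
4. State in advance how to treat a child whose last photograph the panel rates unhealed, or whose images are missing or unreadable. One option is to treat healing as interval-censored after the last visit. Any use of the consultant's date in its place should be flagged and tested in a sensitivity analysis.
5. Say who performs the Visitrak tracing and whether that person knows the dressing.

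The photographs and panel review are already planned, so the cost is wording and some image preparation, with no extra visits or children and no change to 28 per group. The remaining weakness is that panel dates stay partly limited by the bedside decision to end dressing visits, and masking will not be possible in every image.
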